## Abstract

**Methods::**

This is a prospective randomized controlled trial to investigate the efficacy and safety of warm acupuncture in the treatment of type 2 DKD. Participants will be randomly assigned in a 1:1 ratio to either the treatment group (treated with conventional Western medicine) or the control group (treated with warm acupuncture added on the basis of the control group). Both groups will receive 12 weeks of treatment followed by 24 weeks of follow-up. Observation indicators include: 24-hour urinary protein quantification, kidney function, TCM syndrome score and adverse reactions. Finally, SPSS21.0 software will be used to analyze the data.

**Discussion::**

This study will evaluate the efficacy and safety of warm acupuncture in the treatment of DKD, and the results of this trial will provide clinical evidence for the treatment of type 2 DKD.

**Trial registration::**

The TCTR identification number is TCTR20221104004.

## 1. Introduction

Diabetic kidney disease (DKD) is characterized by renal microangiopathy, some patients develop to end-stage renal disease and even need to rely on renal replacement therapy to maintain life.^[1]^ The existing clinical data show that the number of DKD patients worldwide is about 400 million and is expected to be about 592 million by 2035, accounting for about 8% to 10% of the global population. DKD has become one of the important pathogenic factors leading to end-stage renal disease, which seriously threatens the life safety of patients.^[2]^ Therefore, early control of the further development of the disease is extremely important.^[3]^ DKD has become a global public health problem, and there is no targeted treatment at present.^[4]^ There have been many studies on DKD in Western medicine, and the treatment methods have been constantly improving, mainly including conservative treatment such as controlling blood glucose, blood pressure and blood lipids, and renal replacement therapy for end-stage renal disease.^[5]^ However, it is still not ideal in reducing complications, preventing the deterioration process and long-term survival rate.^[6]^ Therefore, how to prevent its further development and improve clinical efficacy has always been the focus of research in the field of DKD, and finding a safe and effective complementary or alternative therapy is also the current trend.^[7]^

Acupuncture and moxibustion are classic complementary and alternative treatments in China.^[8]^ Previous studies have shown that both acupuncture and moxibustion have positive effects on DKD. Acupuncture can reduce the level of proteinuria in type 2 DKD,^[9]^ and moxibustion can reduce the level of serum NO and delay the progress of type 2 DKD.^[10]^ Warm acupuncture is the combination of acupuncture and moxibustion, which combines the advantages of acupuncture and moxibustion and exert a warm effect and the function of acupuncture at the same time.^[11]^ The latest clinical studies have shown that warm acupuncture has a positive effect on improving renal function in patients with DKD.^[12]^ However, there are some problems in this study, such as non-rigorous randomized method, small sample size, and lack of follow-up, which also lead to low evidence strength of research results and limit the application of warm acupuncture in type 2 DKD. Therefore, we will evaluate the clinical efficacy of warm acupuncture in the treatment of type 2 DKD through this randomized controlled trial.

## 2. Materials and methods

### 2.1. Study design

This is a prospective randomized controlled trial to investigate the efficacy and safety of warm acupuncture in the treatment of type 2 DKD. The patients who meet the criteria will be randomly divided into the treatment group and the control group. According to the recommendations of clinical guidelines, the 2 groups of patients will be treated with conventional Western medicine, and the treatment group will be treated with warm acupuncture in addition, follow up for 24 weeks after 12 weeks of continuous treatment. Flow diagram is shown in Fig. 1, and study schedule is shown in Table 1. This experiment will follow the Standards for Reporting Interventions in Clinical Trials of Acupuncture^[13]^ and the comprehensive trial report standard.^[14]^ The study will be completed under the guidance of Standard Protocol Items: Recommendations for Interventional Trials (SPIRIT checklist) 2013 statement.

**Table 1 T1:** Study schedule.

Stage project	Screening period	Treatment period		Follow-up	
	Baseline	8 wk	12 wk	12 wk	24 wk
Record fill	√				
Fulfill inclusion criteria and exclusion criteria	√				
Sign informed consent	√				
Random allocation	√				
Treatment	√	√	√		
Effectiveness observation					
24-hr urinary protein quantification	√	√	√	√	√
Kidney function	√	√	√		√
The TCM Syndrome score	√	√	√		√
Safety assessments					
Routine blood tests	√	√	√		√
Blood test and urinalysis	√	√	√		√
Liver function	√	√	√		√
Electrocardiographic	√	√	√		
Record of adverse event		√	√	√	√

**Figure 1. F1:**
[figure not shown]
Flow diagram.

### 2.2. Ethics and registration

The study protocol complied with the Declaration of Helsinki and Ethical Guidelines for Clinical Research. This study has been reviewed by the Clinical Research Ethics Committee of our hospital and registered on the Thai Clinical Trials Registry (TCTR) (registration number: TCTR20221104004). All patients will be informed of the study plan and potential risks and will not be enrolled until they have provided written informed consent. They will be free to discontinue or withdraw from the trial at any time during the course of the study.

### 2.3. Patients

#### 2.3..1. Diagnostic criteria.

Type 2 diabetes will be defined by the American Diabetes Association criteria.^[15]^ The diagnosis of DKD will be based on the *National Kidney Foundation Kidney Disease Outcomes Quality Initiative Guidelines*.^[16]^

#### 2.3..2. Inclusion criteria.

(1) Meet the diagnostic criteria of type 2 DKD;(2) Age ≥ 18 years old and ≤ 70 years old, regardless of gender;(3) With the 24-hour urinary protein quantification was 0.5 to 3.5 g;(4) With serum creatinine < 265μmol/L (3 mg/dL);(5) Patients voluntarily participated in the trial and signed informed consent.

#### 2.3..3. Exclusion criteria.

(1) Nephropathy due to hypertension or other diseases;(2) Complicated with severe complications and other serious organ dysfunction;(3) Complicated with severe heart disease (NYHA class 3 or above, severe arrhythmia), abnormal liver function (alanine aminotransferase, aspartate aminotransferase ≥ 1.5 times the upper limit of normal value), hematopoietic system diseases (moderate to severe anemia);(4) Complicated with severe infection, diabetic ketoacidosis, hyperkalemia;(5) Complicated with severe mental illness;(6) Pregnant or lactating women;(7) Patients with a history of allergy to one of the drugs used in the study;Subjects participating in clinical trials of other drugs.

#### 2.3..4. Eliminating standard.

(1) Patients with severe adverse events and/or severe complications which will be not suitable for further trial;(2) Patients’ poor compliance affected the judgment of the results;(3) The patient’s condition progressed rapidly during the treatment and the treatment regimen needed to be changed;(4) The subject requested to withdraw from the trial for any reason.

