### 2.4. Sample size

The sample size of this study was calculated based on the change in 24-hour urinary protein quantification (the difference in the standard deviation of the mean value of 24-hour urinary protein quantification before and after treatment) after 12 weeks of treatment, which was 0.87 ± 0.41 in the treatment group according to the results of the pilot study, and the control group was 0.65 ± 0.33. PASS15.0 software was used to estimate the sample size and set α = 0.05, β = 0.10. Finally, 37 participants are needed in each group, and the dropout rate was estimated to be 10%. The total required sample size will be 84 cases, 42 cases in each group.

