### 2.5. Randomization

Eligible patients will be randomly assigned, in a 1:1 ratio, to the treatment group or the control group by means of a central web-based randomization tool. Random numbers will be generated by an independent data statistician using SAS 9.3 software (SAS Institute, Cary, NC). The researcher will enter the patient information on the computer and will be assigned a random number based on which the grouping will be completed. Efficacy assessors will be unaware of the study-group protocol, and data statisticians have no role in the design or conduct of the study.

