### 2.9. Statistical analysis

We will use excel to establish a database, and the outcome data will be statistically analyzed by the full analysis set and per-protocol set. Safety evaluation data will be based on the safety set. The statistical evaluation of full analysis set will follow the intention-to-treat principle. In this study, SPSS21.0 (IBM Company, New York, NY) software will be used for data analysis. The count data will be described by frequency percentage (n (%)) and a Chi-squared test will be used. Measurement data will be described by mean ± standard deviation ($\bar{x}$ ±s) or interquartile range M (P25, P75). One-way analysis of variance will be used for normal distribution comparison between groups, paired sample *t* test will be used for intra-group comparison, and Wilcoxon rank sum test will be used for skewed distribution. *P* < .05 is considered statistically significant.

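### As worded, the eliminating standard in section 2.3.4 conflicts with the intention-to-treat full analysis set promised in section 2.9, and unequal removal can bias the comparison

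*Protocol article*

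**What the plan says.** Section 2.3.4 (Eliminating standard) stands beside the inclusion and exclusion criteria and has four items:

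- Item (1): "Patients with severe adverse events and/or severe complications which will be not suitable for further trial".
- Item (2): patients whose "poor compliance affected the judgment of the results".
- Item (3): a patient whose "condition progressed rapidly during the treatment and the treatment regimen needed to be changed".
- Item (4): "The subject requested to withdraw from the trial for any reason".

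Section 2.5: "Eligible patients will be randomly assigned, in a 1:1 ratio". It masks the efficacy assessors. Section 3 (Discussion) concedes that double blinding was not possible.

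Section 2.9: "the outcome data will be statistically analyzed by the full analysis set and per-protocol set". It adds: "The statistical evaluation of full analysis set will follow the intention-to-treat principle". Section 2.3.4 mentions neither analysis set, and section 2.9 does not mention elimination.

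**The concern.** Intention-to-treat keeps every randomised patient in the group to which chance assigned them. A rule that removes patients for what happens after randomisation works against this, most of all when the reason is linked to the outcome or to the arm. Three features make such a link plausible here.

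- **Outcome.** Item (3) selects patients who did badly. Rapid progression of kidney disease is closely tied to 24-hour urinary protein, the primary outcome in section 2.7.1.
- **Discretion.** Item (2) gives no threshold for compliance and turns on whether the result is thought to be affected. Section 2.5 does not say that whoever makes this judgement is masked.
- **Asymmetry.** Only the treatment arm has needling every other day for 12 weeks (sections 2.6 and 2.1), so that arm has an extra way to be judged non-compliant.

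If eliminated patients leave the trial, their later urine results are never collected. The groups compared at week 12 would then no longer be the groups that were randomised.

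**Working it through.** **Step 1. What does elimination mean?** The document supports more than one reading.

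- Item (3) acts during treatment, and compliance (item 2) can be judged only once treatment has begun. At least these two items therefore apply to randomised patients.
- Items (1) and (4) speak of continuing in, or withdrawing from, the trial. They read as rules for leaving it.
- Item (2) speaks of the judgement of the results. It reads as removal from the analysis.
- No item names the per-protocol set, and no sentence keeps eliminated patients in the full analysis set or takes them out of it.

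If elimination means leaving the full analysis set, it contradicts section 2.9. If it means leaving the trial, set membership survives on paper but the outcome values do not exist. If it concerns only the per-protocol set, there is no conflict, but the text does not say so.

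**Step 2. The plan's own figures on loss.** Section 2.4 needs 37 per group and allows 10% dropout: 37 / 0.9 = 41.1, rounded up to 42 per group and 84 in total. This step reproduces. Ten per cent of 84 is 8.4, so about 8 patients. (Whether 37 follows from the stated inputs is a separate question and has no bearing here.)

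**Step 3. Number of sessions.** 12 weeks × 7 = 84 days. One session every other day gives 84 / 2 = 42.

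**Step 4. Illustration of size.** Inputs from section 2.4: pilot change 0.87, SD 0.41 (treatment) and 0.65, SD 0.33 (control), so the difference is 0.87 − 0.65 = 0.22. Assumptions: change is normally distributed, a larger value is a better response, the unit is grams (section 2.4 gives none; section 2.3.2 uses grams), and the patients lost are exactly the worst 10% of responders.

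Deleting the lowest 10% of a normal variable raises its mean by SD × φ(1.2816) / 0.9 = 0.195 × SD.

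- Treatment arm: 0.195 × 0.41 = 0.080
- Control arm: 0.195 × 0.33 = 0.064

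| Worst 10% lost from | Apparent difference (g) | Change from 0.22 |
|---|---|---|
| Treatment arm only | 0.22 + 0.080 = 0.300 | +36% |
| Control arm only | 0.22 − 0.064 = 0.156 | −29% |
| Both arms | 0.22 + 0.080 − 0.064 = 0.236 | +7% |

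**Step 5. Simulation with no true effect.** 42 per arm, 20,000 runs, common SD √((0.41² + 0.33²)/2) = 0.372, two-sided t test at 0.05, worst responders removed.

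| Removed (one arm / other arm) | Shift in difference (g) | Type I error |
|---|---|---|
| 0 / 0 | about 0 | 5% |
| 4 / 0 | about 0.07 | about 15% |
| 4 / 2 | about 0.03 | about 9% |
| 4 / 4 | about 0 | about 8% |

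The shift of 0.07 is about 30% of the 0.22 design difference. Its sign follows the arm that loses more patients. Equal removal causes almost no shift, but the error rate still rises, because cutting off one tail makes the remaining values look less variable.

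**The case against.** The strongest reply is that the conflict is inferred. Section 2.3.4 never says that eliminated patients leave the full analysis set. Section 2.9 plans two sets, so elimination could govern per-protocol membership or discontinuation alone, and both are compatible with intention-to-treat. This stands. A reader might infer that the eliminating standard defeats the intention-to-treat analysis, or that the trial's result will be biased, and the document supports neither as fact.

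It also stands that one-arm loss is an extreme. The 10% dropout in section 2.4 applies to both arms, and the both-arm figure is only about +7%. Nor need patients lost for compliance, adverse events or withdrawal be the worst proteinuria responders. Greater loss in the treatment arm is possible but not shown: control patients also have a regimen to follow, and they could progress or withdraw more often.

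The handling of missing data may sit in a statistical analysis plan that is not shown, so its absence is not held against the article.

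The reply does not remove the point. The wording of items (1), (2) and (4) leans towards leaving the trial or the analysis. Whether measurements continue after elimination is a rule of conduct, and later analysis methods cannot recover values that were never collected.

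**Conclusion.** The point holds in a conditional form. As worded, section 2.3.4 reads as removing randomised patients from the trial or the analysis on grounds partly tied to outcome and adherence. That conflicts with the intention-to-treat full analysis set in section 2.9. Removal that differs by arm can bias the comparison, and with 42 per arm a few patients are enough to matter.

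The document gives neither the direction nor the size. The range of 0.16 to 0.30 g around 0.22 g marks one-arm extremes under the assumption that every patient lost is among the worst responders. Loss of the same kind in both arms gives about 0.24 g. These figures show sensitivity and are not a forecast. The sections should be reconciled before the analysis, and preferably before recruitment, because uncollected outcomes cannot be restored.

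**What to change.** Reconcile section 2.3.4 with section 2.9 by stating that:

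1. Meeting items (1) to (3) affects membership of the per-protocol set only, and never membership of the full analysis set.
2. Unless the patient withdraws consent for follow-up, the 24-hour urine, kidney function and adverse-event assessments already in Table 1 continue.
3. All randomised patients are analysed in the group to which they were allocated.

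Clinical decisions on stopping or changing treatment are left as they are.

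The cost is a rewording. At the expected 10% dropout, about 8 of 84 patients attend visits that are already scheduled. The downside is that the estimate then includes patients who changed therapy, so the effect may look smaller.

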### 2.4. Sample size

The sample size of this study was calculated based on the change in 24-hour urinary protein quantification (the difference in the standard deviation of the mean value of 24-hour urinary protein quantification before and after treatment) after 12 weeks of treatment, which was 0.87 ± 0.41 in the treatment group according to the results of the pilot study, and the control group was 0.65 ± 0.33. PASS15.0 software was used to estimate the sample size and set α = 0.05, β = 0.10. Finally, 37 participants are needed in each group, and the dropout rate was estimated to be 10%. The total required sample size will be 84 cases, 42 cases in each group.

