### 2.7. Outcome indicators

#### 2.7..1. Primary outcome indicator.

24-hour urinary protein quantification, which will be measured at baseline, weeks 8 and 12 of treatment, and weeks 12 and 24 of follow-up.

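### The primary comparison of 24-hour urinary protein has no stated scale and no baseline adjustment, although entry spans 0.5 to 3.5 g; log-scale ANCOVA would probably be more precise

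*Protocol article*

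**What the plan says.** All references are to the protocol article.

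- **Section 2.4, sample size.** The number was "calculated based on the change in 24-hour urinary protein quantification" after 12 weeks of treatment. The bracketed gloss calls this "the difference in the standard deviation of the mean value of 24-hour urinary protein quantification before and after treatment", which does not define a usable variable. The pilot inputs are given as "which was 0.87 ± 0.41 in the treatment group according to the results of the pilot study" and "the control group was 0.65 ± 0.33", with "set α = 0.05, β = 0.10". No unit is printed; g/24 h is inferred from the entry criterion.
- **Section 2.3.2, inclusion.** "With the 24-hour urinary protein quantification was 0.5 to 3.5 g".
- **Section 2.7.1, primary outcome.** "24-hour urinary protein quantification, which will be measured at baseline, weeks 8 and 12 of treatment", and again at two follow-up visits. Level, change and ratio are all compatible with this text.
- **Section 2.9, analysis.** "One-way analysis of variance will be used for normal distribution comparison between groups", with a Wilcoxon rank sum test for skewed data. No log scale, ratio or baseline term is mentioned, and the quantity to be compared is not named.

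**The concern.** Patients may enter with protein excretion differing by a factor of seven. If treatment lowers protein by a roughly constant percentage, patients with high baselines produce large falls in grams and those with low baselines small ones. A fall of 0.4 g is 0.4/0.5 = 80% of a baseline of 0.5 g but 0.4/3.5 = 11% of a baseline of 3.5 g. Much of the spread in the change then reflects where patients started rather than how they responded.

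An unadjusted comparison carries that spread as noise. A rank test on the change keeps it, because ranks of the change still follow baseline. What is at stake is precision, in a trial with 37 evaluable patients per arm and a baseline measurement that is already collected but not used in the stated between-group test. Because 2.7.1 and 2.9 leave the scale open, it could also be settled after the data are seen.

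**Working it through.** **1. The plan's own figure.** Difference 0.87 − 0.65 = 0.22. Pooled SD = √((0.41² + 0.33²)/2) = √0.1385 = 0.372. For two-sided α = 0.05 and 90% power, n = 2(1.960 + 1.282)² × 0.1385/0.22² = 60.1, so 61 per arm. The stated 37 is not reproduced. The dropout step is right: 37/0.9 = 41.1, so 42. The 37 is a separate matter and serves here only as the reference size. Power at 37: 0.22/(0.372 × √(2/37)) = 2.54; 2.54 − 1.96 = 0.58; power about 72%.

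**2. How much variance could come from baseline.** Assume falls proportional to baseline.
- Uniform baseline on 0.5 to 3.5 g (mean 2.0, SD 0.87). Treatment: (0.87/2.0) × 0.87 = 0.38, and 0.38²/0.41² is about 84% of the change variance (unrounded inputs). Control: (0.65/2.0) × 0.87 = 0.28, about 73%.
- Narrow baseline (mean 2.04, SD 0.49): about 26% and 22%.

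The document gives no baseline distribution, so this range cannot be narrowed.

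**3. Power at 37 per arm, proportional falls.** Simulation, two-sided 5%, 1,500 to 2,000 trials per setting (Monte Carlo error about 1 point). Baseline X is lognormal, truncated to 0.5 to 3.5 g. Week 12 is X·exp(μ + e), e ~ N(0, s²), with μ set so that the mean falls are 0.65 and 0.87. The distribution and s are assumptions.

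| Baseline median / log-SD | s | SD of change, control/treatment | Change | Rank test | Raw-gram ANCOVA | Log ANCOVA |
|---|---|---|---|---|---|---|
| 1.5 g / 0.5 | 0.2 | 0.34/0.40 | 71% | 71% | 99.9% | about 100% |
| 1.5 g / 0.5 | 0.3 | 0.41/0.44 | 57% | 58% | 91% | 96% |
| 1.5 g / 0.5 | 0.4 | 0.51/0.49 | 48% | 48% | 72% | 80% |
| 2.0 g / 0.4 | 0.4 | 0.62/0.56 | 36% | 34% | 43% | 49% |

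Hand check of the log column at median 1.5 g (mean 1.59 g): geometric mean ratio = (1 − 0.87/1.59)/(1 − 0.65/1.59) = 0.453/0.591 = 0.766, log difference 0.266. At s = 0.3: 0.266/(0.3 × √(2/37)) = 3.8; 3.8 − 1.96 = 1.86; power about 97%. At s = 0.4: 2.86 − 1.96 = 0.90; about 82%. Both agree with the table.

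Split of the gain over unadjusted change:
- Median 1.5 g, s = 0.3: 91 − 57 = 34 points from adjustment, 96 − 91 = 5 from the log scale.
- Median 1.5 g, s = 0.4: 24 and 8.
- Last row: 7 and 6.

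**4. Power if falls are additive** (pilot means and SDs, independent of baseline, week 12 floored at 0.05 g).

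| Baseline median / log-SD | Change | Unadjusted log ratio | Log ANCOVA |
|---|---|---|---|
| 1.5 g / 0.5 | 60% | 41% | 57% |
| 2.0 g / 0.4 | 69% | 46% | 61% |

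Across runs the unadjusted ratio loses about 19 to 24 points and log ANCOVA about 3 to 9.

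**5. The floor.** Protein cannot fall below zero. A fall of 0.65 g is impossible only for baselines of 0.50 to 0.65 g: 0.15/3.0 = 5% of the range by width, and about 0 to 4% of patients under the baselines in the table. A fall of 0.87 g is impossible below 0.87 g: 0.37/3.0 = 12% by width, about 2 to 13% of patients.

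**The case against.** The strongest reply is that nothing here is invalid. Randomisation balances baseline in expectation, so an unadjusted comparison is unbiased, and reporting grams is a legitimate choice. A baseline covariate may also be specified in a statistical analysis plan that is not shown. The first two points stand: this is a matter of efficiency and definition. The third stands only in part, because 2.9 does state a between-group method, and it is unadjusted.

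Two further objections carry weight. Only the s = 0.2 setting reproduces the pilot SDs (0.34/0.40 against 0.33/0.41); the other rows describe noisier responses than section 2.4 implies. Every large gain also assumes proportional falls, and the document gives no baseline distribution, log-scale SD or correlation of change with baseline to support that.

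Stronger readings are tempting and should be resisted:
- *The primary variable is defined as absolute change.* Only the sample-size section speaks of change; 2.7.1 and 2.9 do not.
- *Low-baseline patients cannot respond on this scale.* That holds for a narrow band at the bottom of the range, and some individuals being unable to reach a mean does not invalidate a difference in means.
- *A ratio scale by itself recovers the precision, whatever baseline adjustment is made.* Raw-gram ANCOVA obtains most of the gain, and if falls are additive an unadjusted ratio loses precision.

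**Conclusion.** The point holds in a limited form. The scale of the primary comparison is not fixed, the one variable named for sizing is a change, and the stated tests ignore baseline despite a seven-fold entry range.

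Under proportional falls and the assumed baselines, power at 37 per arm is about 36 to 73% for unadjusted change, 43 to 99.9% for raw-gram ANCOVA and 49 to 100% for log ANCOVA. Adjustment gives most of that gain, although in the least favourable setting the split is nearly even. The log scale adds up to about 9 points. Under additive falls, log ANCOVA costs about 3 to 9 points.

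The size of the benefit therefore depends on data that the sponsor holds from the pilot and the document does not show. The exchange is favourable unless those data point to additive falls. The floor is a minor point.

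**What to change.** In 2.7.1, define the primary comparison as week-12 24-hour urinary protein on the log scale. In 2.9, analyse it by ANCOVA with log(baseline) as covariate, not as an unadjusted ratio, and report a geometric mean ratio with 95% CI. Keep the absolute change in g/24 h as a secondary figure so that results can be set beside the pilot. In 2.4, state the unit and replace the bracketed gloss with a clear definition of the variable.

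Before fixing the scale, check in the pilot data whether falls grow with baseline, and obtain the log-ratio SD. If falls look additive, ANCOVA in grams is the natural alternative and still uses baseline.

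The cost is wording, to be settled before any data are analysed, with no new measurements or patients. Results will be read as percentages rather than grams, the pilot figures must be re-expressed on the log scale, and there is the modest loss of power noted above if falls are in truth additive.

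### 37 per group does not give the stated 90% power: on the protocol's own pilot figures it gives about 71% two-sided, or 81% one-sided

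*Protocol article*

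**What the plan says.** All inputs and the result are printed in section 2.4 (Sample size) of the protocol article.

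- **Basis:** "The sample size of this study was calculated based on the change in 24-hour urinary protein quantification", taken after 12 weeks of treatment.
- **Treatment group:** "which was 0.87 ± 0.41 in the treatment group according to the results of the pilot study".
- **Control group:** "the control group was 0.65 ± 0.33".
- **Error rates:** "PASS15.0 software was used to estimate the sample size and set α = 0.05, β = 0.10". Whether α is one- or two-sided is not stated.
- **Result:** "Finally, 37 participants are needed in each group, and the dropout rate was estimated to be 10" (per cent).
- **Total:** "The total required sample size will be 84 cases, 42 cases in each group".

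Section 2.5 (Randomization) sets 1:1 allocation. Section 2.9 (Statistical analysis) plans a one-way analysis of variance between the groups, with significance at P below .05.

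**The concern.** The pilot difference is 0.22 and the two SDs average out (root mean square) to about 0.37, a standardised effect of about 0.59. For an effect of that size, 37 per group looks too few for 90% power at α = 0.05, so the printed β and the printed sample size cannot both be right.

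This calculation sizes the trial for its primary outcome. The printed β tells readers that, if the pilot effect is real, the trial has a one-in-ten chance of missing it. If the true chance is nearer three in ten, a non-significant result carries much less evidence against warm acupuncture than the protocol implies. The introduction criticises the earlier warm acupuncture study for its small sample, among other faults, so the power claim also bears on the trial's own rationale.

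**Working it through.** **Inputs (section 2.4):** changes 0.87 (SD 0.41) and 0.65 (SD 0.33); difference 0.22; α = 0.05; β = 0.10; 1:1 allocation (section 2.5). Sidedness is not stated, so both cases are computed. For two groups, the one-way analysis of variance in section 2.9 is the two-sided pooled t test, so two-sided is the natural reading.

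**Step 1. Dropout allowance.** 37 / 0.9 = 41.1, rounded up to 42 per group, 84 in total. This reproduces. Any error is in the 37.

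**Step 2. Sample size per group.** Normal approximation:

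n = (z_α + z_β)² × (SD₁² + SD₂²) / difference²

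(0.41² + 0.33²) / 0.22² = (0.1681 + 0.1089) / 0.0484 = 0.2770 / 0.0484 = 5.723

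| α = 0.05 | Power | (z_α + z_β)² | n, normal | n, noncentral t |
|---|---|---|---|---|
| two-sided | 90% | 10.507 | 60.1, so 61 | 62 |
| one-sided | 90% | 8.564 | 49.0 (just above), so 50 | 50 |
| two-sided | 80% | 7.849 | 44.9, so 45 | 46 |
| one-sided | 80% | 6.183 | 35.4, so 36 | 37 |

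Neither 90% row gives 37. The two-sided requirement is 62 / 37 = 1.68 times the stated number.

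**Step 3. Power at the stated sizes.** By the normal approximation at 37 per group, the standard error is √(0.2770 / 37) = 0.0865 and 0.22 / 0.0865 = 2.543. Two-sided power is Φ(2.543 − 1.960) = 72.0%. One-sided power is Φ(2.543 − 1.645) = 81.5%. The noncentral t gives:

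| Evaluable per group | Two-sided | One-sided |
|---|---|---|
| 37 | 70.8% | 80.9% |
| 42 (no dropout) | 76.3% | 85.1% |

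Pooled and Welch versions agree to within 0.1 percentage point.

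**Step 4. Difference detectable with 90% power at 37 per group, two-sided.** Normal: √10.507 × 0.0865 = 0.280. Welch t: 0.284. The ratio 0.284 / 0.22 = 1.29, so the effect would have to be 29% larger than in the pilot.

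**Step 5. Could another reading give 37?**

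- *One SD for both arms (t test, 90% power).* With 0.33: 49 two-sided, 40 one-sided. With 0.41: 74 and 61. Even the smallest of these exceeds 37.
- *One-sided α 0.05 with 80% power (t test).* Exactly 37, but this contradicts β = 0.10.
- *One-sample normal formula with SD 0.41, two-sided, 90% power.* 10.507 × 0.1681 / 0.0484 = 36.5, rounded up to 37, but this leaves out the second group's variance.
- *One-sided α of 0.10 with 90% power.* 38 (normal), and it contradicts α = 0.05.
- *Baseline-adjusted analysis.* 37 would suffice if adjustment removed about 1 − 37/62 = 40% of the variance (correlation about 0.62). Section 2.4 states no adjustment and section 2.9 plans an unadjusted analysis of variance.

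Every route to 37 changes or omits something that section 2.4 states.

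**The case against.** Several points can fairly be made for the protocol.

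- **Sidedness is not stated.** On a one-sided reading, power at 37 is 81% and the risk of missing the effect is 19%, not 29%. This stands as a caveat on size. The planned analysis of variance supports the two-sided reading, and 90% is missed on either.
- **42 per group are randomised, and the full analysis set follows intention to treat.** If outcomes are obtained for everyone, power is 76% two-sided or 85% one-sided. That narrows the gap without closing it. The protocol itself names 37 as the number required for β = 0.10.
- **The cause is not known.** One-sided α with 80% power gives 37, but so does a one-sample formula with SD 0.41. The document does not show which route was taken, so no specific software setting can be blamed. The mismatch does not depend on the cause.
- **Units and definition.** Section 2.4 gives no unit, and its description of the sizing quantity is garbled. Grams is inferred from the inclusion criterion in section 2.3. Reading the ± figures as SDs of change agrees with the mean ± SD convention of section 2.9. If they were standard errors, the SDs would be larger and the shortfall greater. The power figures do not depend on the unit.
- **This is a condensed article and any analysis plan is not shown.** That excuses omissions. Here the means, SDs, α, β and n are all printed and disagree, which no further document can repair.

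**Conclusion.** The concern holds. On the printed pilot figures, 90% power needs 62 evaluable per group two-sided or 50 one-sided, against 37 stated. The stated size gives about 71% power two-sided (81% one-sided), and at most 76% (85%) if nobody drops out. The two-sided risk of missing the pilot effect is about 29%, nearly three times the 10% claimed.

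This rests on three assumptions: the ± figures are SDs of the change, the groups are compared by an unadjusted two-sample test as section 2.9 plans, and α is two-sided for the headline figure. The first two are the plain reading of the text. Dropping the third reduces the shortfall but does not remove it. How 37 was obtained remains unknown.

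**What to change.** Correct section 2.4; the statement of 90% power cannot stand beside 37 per group.

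**Preferred, keeping 84 patients.** State that α is two-sided at 0.05. State that 37 evaluable per group gives about 71% power for a difference of 0.22 (SDs 0.41 and 0.33) and reaches 90% only for a difference of about 0.28. Give the unit. The cost is a change of wording and a less favourable stated power; no patients are added.

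A baseline-adjusted primary analysis could recover part of the loss. It would restore 90% only if baseline explained about 40% of the variance in change, and the protocol offers no figure to support that. It should not be used to justify the 37 without pilot data.

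**Alternative, if β = 0.10 is a firm design target.** Enlarge the trial. Two-sided: 62 / 0.9 = 68.9, so 69 per group and 138 in total, 54 more than planned. If a one-sided test was really intended, that must be stated and justified: 50 / 0.9 = 55.6, so 56 per group and 112 in total, 28 more than planned.
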